# Protocol for SonoSpeech Cleft Pilot: a mixed-methods pilot randomized control trial of ultrasound visual biofeedback versus standard intervention for children with cleft lip and palate

**DOI:** 10.1186/s40814-022-01051-x

**Published:** 2022-04-27

**Keywords:** Cleft lip and palate, Articulation intervention, Ultrasound visual biofeedback

## Abstract

**Background:**

Children with cleft lip and palate can continue to have problems producing clear speech after surgery. This can lead to social, emotional, and educational challenges. Typical treatment involves teaching children the correct tongue movements to produce speech sounds. This is known as articulation intervention. However, this intervention is challenging because the tongue is hidden from view and movements are difficult to see and describe. This pilot randomized control trial will try a new treatment, ultrasound visual biofeedback (U-VBF) versus standard articulatory intervention for children with cleft lip and palate, as comparison. Feasibility outcomes will be determined.

**Methods/design:**

The Sonospeech project will enroll up to 40 children with cleft lip and palate aged 4;6 to 16 in a mixed-methods randomized controlled trial with blinded assessors. Children will receive either six sessions of U-VBF or articulation intervention. The primary goals of this pilot are to assess the feasibility and inform the design of a full-scale RCT of U-VBF for children with cleft speech characteristics. This will be achieved by determining the following outcome measures: recruitment/attrition rates; measures of pre-post follow-up completion; and acceptability of the randomization and interventions to families.

**Discussion:**

Larger trials of speech interventions for children with cleft lip and palate are needed. This pilot/feasibility study will determine whether a larger randomized control trial comparing ultrasound and articulation interventions is feasible.

**Trial registration:**

ISRCTN, ISRCTN17441953. Registered 22 March 2021. See Table 2 in Appendix 1 for all items.

## Background

Cleft lip and palate (CLP) is the most common congenital craniofacial abnormality, occurring in 1 in 700 live births, depending on geographical area [1]. Problems producing intelligible speech occur in CLP, even after surgery to repair the palate, and in some children cleft speech characteristics (CSC) persist, requiring intervention from a speech and language therapist (SLT) [2]. This unintelligible speech has adverse social and educational consequences, with the speech of children with CLP rated as more likely to belong to someone who is associated with negative stereotypes about appearance and socialization [3].

Standard treatment in Scotland is articulation intervention (AI), or motor-phonetic intervention, although there is also recent research supporting linguistic-phonological therapy approaches [4]. The articulation intervention approach involves teaching children correct placement for their articulators (primarily the tongue) through verbal description and demonstration [5]. AI is a challenging intervention for both the clinician and the patient because speech movements are both difficult to see and describe, due to the main articulator, the tongue, being largely hidden from view. This problem can be circumvented by using instrumental articulatory techniques which view and measure the articulators directly.

Over the last few decades electropalatography (EPG) has dominated the literature as the instrumental technique of choice for people with cleft lip and palate [6]. EPG measures tongue-palate contact using an artificial palate with electrodes embedded in it [7]. This real-time dynamic image of tongue-palate contact can be used as a biofeedback tool to teach patients about correct placement of the tongue. However, a Cochrane review of EPG by Lee and colleagues [6] found that only one study met inclusion criteria. Despite a large number of studies using EPG, most were small n or case studies. It is likely that larger studies using EPG are sparse because of practical issues with using this tool. Each patient requires an expensive custom-made palate; moreover, this custom-made palate only fits for a limited time period due to changing dentition and planned surgeries.

In contrast, ultrasound visual biofeedback (U-VBF) is growing in popularity as biofeedback tool for children with speech disorders [8]. U-VBF holds several practical advantages over EPG: it is cheaper and does not require individualized equipment. The one-off outlay cost of an ultrasound system that is suitable for speech therapy is approximately $6,000 [9], initial outlay for EPG is similar, but in addition each patient requires an EPG plate costing between $300-$570, not including the dental impression cost [7]. Moreover, while EPG images only tongue-palate contact from the alveolar region to the boundary of the hard and soft palate, U-VBF images from near the tongue tip to the root, with pharyngeal articulations, common in CLP, clearly visible. This makes U-VBF arguably the technique of choice for CLP [10]; yet, it is relatively new to the Speech and Language Therapy clinic. This is because it is only now that ultrasound systems for measuring articulation provide fast enough frame rates at an affordable cost.

A recent study showed that ultrasound can be used to identify all of the CSC described in the instrumental literature and that ultrasound assessment has better reliability than traditional perceptual approaches [11]. However, U-VBF has to our knowledge only been used in one small study with two participants with CLP [12]. In that study the U-VBF treatment was effective for one of the children, aged 6;2, who achieved accurate production of target sounds and generalized them to untreated words. In children with other types of speech sound disorders, U-VBF shows positive outcomes for the majority of children and it is particularly useful for establishing new articulations [8]: an area of particular difficulty in CLP [5]. U-VBF is therefore potentially a useful tool for establishing new articulations in children with CLP. The aim of this study is therefore to assess the feasibility and inform the design of a full-scale RCT of U-VBF for children with cleft speech characteristics. Key objectives and success criteria for proceeding to full trial are given below. If these are met, a full-scale RCT will proceed using a similar design. Questionnaires and focus groups will provide qualitative data from patients and carers. If this points to specific improvements that can be made in the design, and they do not interfere with the aims of the large-scale study, they will be implemented.

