### Research questions

No definitive comparisons of the interventions will be undertaken. The feasibility of a full-scale RCT will be determined by evaluating a number of objectives against set success criteria (bulleted below) taken from a similar pilot RCT of children with speech disorders [13]:

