#### Objectives

To determine recruitment and attrition rates.75% of children and their families identified agree to participate.75% of children allocated in each group are retained for the duration of the study.To measure pre-post and follow-up outcome measure completion.75% of outcome measures are completed.To measure within-session outcome measure completion.Data is reported from 75% of intervention sessions.To determine acceptability of randomization to children and their families.75% of children and their families rate randomization as acceptable in a questionnaire.To determine the acceptability of ultrasound visual biofeedback as an assessment tool (both groups) and intervention tool (U-VBF group).75% of children and their families rate ultrasound as an acceptable technique in a questionnaire.Focus group analysis contains more positive than negative themes regarding acceptabilityTo measure adherence to the treatment protocol.75% of sessions reach the minimum dosage of 100 trials in both treatment arms.

In addition to the quantitative objectives measuring acceptability using questionnaires, this data will be validated using focus group interviews with parents and participants who volunteer. The interviews will be analyzed inductively to identify emergent themes and deductively, using the Theoretical Framework of Acceptability [14].

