## Discussion and summary

This pilot feasibility study will determine whether a full-scale randomized control trial comparing ultrasound visual biofeedback to treatment as usual (articulation intervention) for the treatment of cleft speech characteristics is feasible. Prior studies such as [21] suggest that children with CLP can tolerate ultrasound recordings and studies such as [14] suggest good retention in ultrasound intervention, with only one child in this study lost to follow-up. We therefore predict that the objectives outlined above will be met, and if this is the case a full-scale, adequately powered, multi-center RCT will be warranted. Within this planned larger RCT, we hypothesize that U-VBF will show quicker acquisition of speech sounds in error, leading to shorter time in intervention, reduced frustration for patients, and cost savings. Nevertheless, there are some potential limitations to the current study. Firstly, it is not known how acceptable randomization will be to patients and carers, and it is possible that carers will express a preference for the trial intervention, given the novelty of the technology used in U-VBF [23]. To mitigate this, patients will be offered U-VBF at the completion of the study, if their speech errors remain. A previous study trialing a similar technology-based intervention with children with Down syndrome showed that no children were lost to follow-up in either arm of the trial when this was offered [32]. A further limitation of the current study, which cannot be completely mitigated, is a potential preference from the treating clinicians for one intervention over the other, in particular the trial intervention. This could lead to increased outcomes in the trial intervention, which are not due to the visual biofeedback per se, but more to increased motivation in the intervention sessions [33]. Finally, a recent move towards more use of telehealth due to the COVID-19 pandemic, means that U-VBF is disadvantaged compared to articulation intervention, because it is a behavioral intervention which requires hardware and therefore only be can only be carried out in person, rather than over video-conferencing. It therefore currently may be more difficult to recruit to a trial which involves travel to a hospital or university.

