In conclusion, this feasibility study will determine whether a larger trial comparing U-VBF and Articulation Intervention is both feasible and acceptable to patients and their carers. Notwithstanding the limitations, we predict that achieving the success objectives related to recruitment, retention, and acceptability outlined above will motivate a full scale RCT which in turn seeks to determine whether U-VBF shows improved outcomes over treatment as usual for speech disorders associated with cleft lip and palate.

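### A count of positive against negative focus-group themes is a pass/fail success criterion, although its result depends on how the analyst groups the themes

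*Protocol article*

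**What the plan says.** Three places in the protocol article make the listed criteria the basis for going on.

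- **Background:** "Key objectives and success criteria for proceeding to full trial are given below", and then "If these are met, a full-scale RCT will proceed using a similar design".
- **Research questions:** "The feasibility of a full-scale RCT will be determined by evaluating a number of objectives against set success criteria".
- **Discussion and summary:** a full trial is called warranted on the same condition, in a sentence shortened here: "We therefore predict that the objectives outlined above will be met, and if this is the case a full-scale, adequately powered, multi-center RCT will be".

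The Objectives section gives eight criteria under six objectives. Seven are 75% thresholds: recruitment ("75% of children and their families identified agree to participate"), retention ("75% of children allocated in each group are retained for the duration of the study"), outcome completion, within-session data, questionnaire acceptability of randomization, questionnaire acceptability of ultrasound, and dosage. The eighth stands beside the ultrasound questionnaire threshold under the same objective: "Focus group analysis contains more positive than negative themes" regarding acceptability.

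The paragraph after the list gives the focus groups a different job, which is to validate the questionnaire data. It says that they involve parents and participants who volunteer, and that the analysis will be both inductive and deductive, the latter under the Theoretical Framework of Acceptability. The section on intervention acceptability and qualitative evaluation adds that parents or carers and children over 12 are invited, that each group has up to 10 participants, and that a research assistant carries out the thematic analysis, described there as inductive.

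The last paragraph of the Discussion predicts that "achieving the success objectives related to recruitment, retention, and acceptability outlined above will motivate a full scale RCT".

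**The concern.** A progression criterion should give the same answer to anyone who applies it to the same data. The 75% criteria come close to this, because each has a countable unit and a denominator. The theme count has neither. In an inductive analysis the themes do not exist until the analyst forms them, and two competent analysts can divide the same material into different numbers of themes. Where the positive and negative counts are close, that choice decides whether the criterion is met.

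The count also measures the wrong quantity. A theme raised by one participant weighs as much as one raised by all ten in a group, and a minor irritation weighs as much as a reason to refuse the treatment. The people heard are volunteers, whereas the questionnaire goes to families generally and is also offered to those who drop out.

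What is at stake is the pilot's main conclusion, since feasibility is judged against this list.

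**Working it through.** **Inputs from the protocol article**
- Criterion: number of positive themes P must exceed number of negative themes N (Objectives). A tie misses.
- Themes are inductive, so P and N are not fixed in advance. No counting rule is shown, and the criterion does not say whether inductive or deductive themes are counted.
- Target: 20 children per arm, 40 in total.
- The article states no expected number of themes, so the counts below are assumptions for illustration.

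**Step 1: effect of merging themes**
- P = 5, N = 4: 5 > 4, met. Merge two positive themes: P = 4, N = 4, 4 > 4 is false, missed.
- P = 3, N = 3: 3 > 3 is false, missed. Merge two negative themes: P = 3, N = 2, 3 > 2, met.

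The transcripts are the same before and after each merger. One grouping decision changes the result, and it can do so in either direction.

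**Step 2: effect of the number of themes**
Suppose each of k themes is independently positive with probability 0.6 (an assumption). The chance of meeting the criterion is P(X > k/2), with X binomial(k, 0.6).

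| k | needed | chance of meeting |
|---|---|---|
| 5 | 3 | 0.683 |
| 6 | 4 | 0.544 |
| 9 | 5 | 0.733 |
| 10 | 6 | 0.633 |

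With the underlying balance of views held fixed, the chance runs from 0.54 to 0.73 according to how finely the themes are cut. Much of the difference between odd and even k arises because only an even number can tie. From 5 to 9 themes the chance rises by 0.733 − 0.683 = 0.050, and from 6 to 10 by 0.633 − 0.544 = 0.089. Real themes are not independent draws, so this shows dependence on grouping and does not forecast the result.

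**Step 3: contrast with the questionnaire criterion**
If all 40 families answer, the 75% threshold is 0.75 × 40 = 30 favorable answers. The unit is the family. How answers are grouped afterwards cannot change the count.

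**Step 4: the closing sentence against the list**

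| Criterion under Objectives | Named in the closing sentence |
|---|---|
| Recruitment | yes |
| Retention in each group | yes |
| Outcome completion | no |
| Within-session data | no |
| Acceptability of randomization (questionnaire) | yes |
| Acceptability of ultrasound (questionnaire) | yes |
| Acceptability of ultrasound (theme count) | yes, as acceptability |
| Dosage | no |

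The sentence leaves out three of the eight criteria. The theme count falls under both wordings, so it does not cause the mismatch. The two points are separate.

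**The case against.** The best defense is that the theme count is not meant to stand alone. It sits beside a questionnaire threshold, the focus groups are there to validate that questionnaire, and a full protocol may hold a coding frame and a counting rule that a condensed article omits. The article also says that its success criteria come from a similar pilot trial. And the same focus groups can properly inform both acceptability and design, so using them for both is no conflict.

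Much of this stands. The absence of a coding frame is not the point here, and the dual use of the qualitative data is not a fault. But the article itself states the criterion and places it in the list on which progression rests. A counting rule would make the count more reproducible, yet it would still not reflect how many families hold a view or how strongly.

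Two stronger readings are tempting, and the document supports neither.

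- **Two opposed go rules.** A reader might set the closing sentence against the Background and conclude that the same data could give opposite decisions. The closing sentence is a prediction about what will motivate a full trial. It does not say that only the named objectives count. The Background, the Research questions section and the preceding paragraph of the Discussion all rely on the whole list.
- **A veto for every criterion.** A reader might take the Background to mean that one miss stops the full trial. It says what follows if the criteria are met, which is a sufficient condition. It does not say what follows if some are missed, and a condensed article may leave that to the full protocol. The chance of meeting all criteria jointly would therefore measure the strictness of a rule that the article does not state.

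Whether outcome completion, session data and dosage should carry less weight than the other criteria is a design choice, and nothing here requires it.

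**Conclusion.** The point holds for the theme count. As written, the criterion can turn on a single decision to split or merge themes, shown by 5 v 4 becoming 4 v 4 and by 3 v 3 becoming 3 v 2. The consequence is that the pilot moves between all listed criteria met and one missed. The document does not support calling that a move from go to no-go.

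The conclusion rests on two things that the article states: the themes are formed inductively, and the criterion is in the progression list. It matters when the positive and negative counts are close. With a wide margin, regrouping would not change the answer. How close they will be cannot be known from the article.

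The closing sentence of the Discussion is a minor inconsistency in wording, to be tidied in the same edit.

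**What to change.** In Objectives, remove the theme count as a pass/fail criterion. Keep the two 75% questionnaire thresholds, for randomization and for ultrasound, as the acceptability criteria. State that the focus groups will be reported under the Theoretical Framework of Acceptability, as already planned, to explain the questionnaire results and to guide changes to the full trial's design.

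In the last paragraph of the Discussion, replace the short list with a reference to all the success criteria under Objectives, so that it matches the Background, the Research questions section and the paragraph before it.

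The cost is a change of wording, best made before the focus groups are analyzed, and reported to the registry and the ethics committee as the dissemination section provides for protocol changes. No new data or staff are needed. The small downside is that the qualitative strand no longer has a numerical threshold.

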## Methods/design

### Aims

The aim of this study is to assess the feasibility and inform the design of a full-scale RCT of U-VBF for children with cleft speech characteristics. The primary aim of U-VBF is to enable learning of new articulatory gestures (new speech sounds), with secondary aims of improving intelligibility and health-related quality of life.

### Design and setting

A single-center mixed-methods two-arm parallel group pilot randomized controlled trial design will be used. The study is a single blind pilot randomized controlled trial, with control offered U-VBF therapy at the end of the study. A qualitative study (focus group) of the acceptability of both interventions and the study design will also be undertaken. All intervention will take place at the speech and language therapy hub in the Royal Hospital for Children in Glasgow. Eligibility screens and pre- and post-intervention assessments will take place either in person in a university clinic room or via telehealth (Zoom^TM^ or Microsoft TEAMS^TM^). The roles and responsibilities are outlined in Appendix 2.

### Research questions

No definitive comparisons of the interventions will be undertaken. The feasibility of a full-scale RCT will be determined by evaluating a number of objectives against set success criteria (bulleted below) taken from a similar pilot RCT of children with speech disorders [13]:

#### Objectives

To determine recruitment and attrition rates.75% of children and their families identified agree to participate.75% of children allocated in each group are retained for the duration of the study.To measure pre-post and follow-up outcome measure completion.75% of outcome measures are completed.To measure within-session outcome measure completion.Data is reported from 75% of intervention sessions.To determine acceptability of randomization to children and their families.75% of children and their families rate randomization as acceptable in a questionnaire.To determine the acceptability of ultrasound visual biofeedback as an assessment tool (both groups) and intervention tool (U-VBF group).75% of children and their families rate ultrasound as an acceptable technique in a questionnaire.Focus group analysis contains more positive than negative themes regarding acceptabilityTo measure adherence to the treatment protocol.75% of sessions reach the minimum dosage of 100 trials in both treatment arms.

In addition to the quantitative objectives measuring acceptability using questionnaires, this data will be validated using focus group interviews with parents and participants who volunteer. The interviews will be analyzed inductively to identify emergent themes and deductively, using the Theoretical Framework of Acceptability [14].

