### Participants

#### Inclusion criteria

Children managed by the Scottish Cleft Lip and Palate service aged 4;6 to 16 will be identified and recruited when attending SLT clinics at the Royal Hospital for Children in Glasgow. Invitation letters containing the complete study information sheets will be sent to families. Inclusion criteria regarding age and cleft-type are broad to reflect current clinical practice; however, inclusion criteria for type of cleft speech characteristic are narrower to ensure children are likely to benefit from either U-VBF or the control intervention. Children are eligible if they have at least one speech error that would normally be a candidate for articulation intervention. This will be assessed by a researcher SLT who is not involved in the therapy. We aim to recruit 20 children to each arm of the trial. Recruitment will stop once the target number of participants is recruited and within two years from the beginning of the study. No interim analyses will be performed before all data is collected. In summary, the inclusion criteria are: children aged 4;6 to 16, with any oral cleft-type, who have at least one speech error which requires articulation intervention.

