### Eligibility/baseline assessments

We will screen potential participants from case-notes and invite them to attend an initial screening and baseline assessment. The person carrying it out will obtain consent, ensuring the participants and their families have had time to read, understand, and discuss the information about the study, prior to any assessment or procedures. The person carrying out this assessment will not be involved in the therapy. This assessment will be either in person or via video conferencing, with in-person preferred. Screening assessment will comprise the British Picture Vocabulary Test 3 [15] to screen for adequate receptive vocabulary. This test does not require verbal responses or assess speech production, instead participants point to responses. The screening will also include a speech assessment protocol to determine whether patients present with at least one cleft speech characteristic which would be amenable to both U-VBF and the control intervention. This assessment protocol comprises the Diagnostic Evaluation of Articulation and Phonology [16] articulation and phonology subtests and an ultrasound tongue imaging protocol designed in a previous project [11] to identify covert speech errors from consonants at all places of articulation and sentences from the GoS.SP.aSS.’98/ CAPS-A [17] (Appendix 1). Families who opt for the assessment over video-conferencing will complete the same assessments, but the ultrasound tongue imaging protocol will be replaced with an audio-perceptual assessment of the same materials^1^.

There are some limitations that may arise as a result of online video assessment, such as detecting sounds where the articulators are not visible (e.g., /k/ or /g/) or detecting high-frequency sounds (e.g., /s/ or /ʃ/), despite overall good agreement rates reported for online articulation assessments [18]. However, we retain this option for participants to address potential national and local pandemic regulations [19] during which travelling to a university for assessment is not classified as essential travel.

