### Intervention acceptability measures and qualitative evaluation

Families will complete a questionnaire about the acceptability of both interventions at the end of the study. These questionnaires will also be offered to families of participants who drop out of the study. Participant retention will be promoted by dedicating time to discuss any questions and problems that may have arisen for the participant and their family at the start of each session and by offering further ultrasound or articulation intervention after the final follow-up if indicated. Parents/carers and children over 12 will be invited to join focus groups to discuss their experiences of taking part in the trial and to contribute to planning a larger trial. Focus groups will be run by the PI and an RA online using the topic guide available in a publically accessible folder available at [30] (or via DOI 10.15129/f65343c4-7781-44fe-9b00-516d4597efac). Each focus group will include up to 10 participants. Responses to the focus groups will be analyzed by an RA using thematic analysis, following the same methods employed in a similar study with children with cerebral palsy [31], that is, inductive thematic analysis.

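### The recruitment success criterion can be met by a pilot that failed to recruit, because it counts agreement before eligibility is known and is tied to neither the target of 40 nor the two-year limit

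*Protocol article*

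**What the plan says.** The Background section makes the success criteria the trigger for the next trial: "If these are met, a full-scale RCT will proceed using a similar design". The Research questions section likewise says that feasibility is judged against them.

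The recruitment criterion, under Objectives, is "75% of children and their families identified agree to participate". A separate criterion there is "75% of children and their families rate randomization as acceptable in a questionnaire".

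The order of events comes from several sections:

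- Eligibility/baseline assessments: "We will screen potential participants from case-notes and invite them to attend an initial screening and baseline assessment". Consent is taken at that visit before anything is assessed. The receptive vocabulary test (BPVS-3) and the speech protocol follow.
- Speech target selection: a child must score below 30 PTC at baseline to be eligible.
- Randomization: allocation comes after baseline.

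The target and the time limit appear under Inclusion criteria and again under Analyses and statistical power: "We aim to recruit 20 children to each arm of the trial" and "Recruitment will stop once the target number of participants is recruited and within two years from the beginning of the study". The Abstract treats 40 as a ceiling on enrolment.

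On questionnaires, the section on intervention acceptability describes one given to families at the end of the study, and adds: "These questionnaires will also be offered to families of participants who drop out of the study".

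**The concern.** Recruitment is the first objective listed. The Discussion itself expects that travel may make recruiting harder and says that "it is not known how acceptable randomization will be to patients and carers". A go/no-go rule on recruitment should therefore fail when too few children are randomized in the time available.

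The stated rule is a bare proportion. Its numerator is agreement, so a family that consents and is then found ineligible counts as a success. Its denominator is undefined: *identified* could mean everyone whose notes were looked at, or only those invited after the case-note screen. No minimum number and no period are attached. Slow accrual, a small pool and heavy post-consent ineligibility can each coexist with a pass, and the full trial would then go ahead on a design whose accrual had not been tested.

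**Working it through.** **Inputs from the article.** Target: 2 arms × 20 = 40, which agrees with the target sample size in Appendix 1. Agreement threshold: 75%. Recruitment limit: two years. No power calculation is given, so there is none to reproduce.

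**Input assumed.** The proportion *s* of consenting children who then prove ineligible is not stated. I use 0%, 20% and 50%.

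**Step 1: does any other criterion catch low numbers?** The remaining quantitative criteria (retention in each group, outcome completion, within-session data, acceptability of randomization, acceptability of ultrasound, dosage reached) are all proportions with a 75% threshold. The focus-group criterion compares positive with negative themes. None refers to a number randomized or to a period.

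**Step 2: apply the recruitment rule exactly as written.**

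- 8 identified, 6 agree: 6/8 = 75%, a pass. At most 6 of 40 are randomized (6/40 = 15%), or 6 × 0.5 = 3 if half prove ineligible.
- 20 identified, 15 agree: 15/20 = 75%, a pass. At most 15 of 40 are randomized (37.5%), or 15 × 0.5 = 7.5, so about 7 or 8, if half prove ineligible.

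**Step 3: families needed to randomize 40 at exactly 75% agreement.** Identified needed = 40 / (0.75 × (1 − s)), rounded up.

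- s = 0: 40/0.75 = 53.3, so 54
- s = 0.20: 40/(0.75 × 0.80) = 40/0.60 = 66.7, so 67
- s = 0.50: 40/(0.75 × 0.50) = 40/0.375 = 106.7, so 107

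The criterion reads 75% in all three cases, while randomized/identified falls from 75% to 60% to 37.5%.

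**Step 4: chance of passing with a small pool.** Suppose the true agreement rate is 60% (assumed), and let X be binomial with n families identified. The exact probability of reaching 75% is:

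- n = 8: P(X ≥ 6) = 0.315
- n = 20: P(X ≥ 15) = 0.126
- n = 54: P(X ≥ 41) = 0.011

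So the fewer families the service can find, the easier it is to pass this rule by chance.

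**Step 5: who rates randomization.** The only questionnaire recipients described are families at the end of the study and families of participants who dropped out. Both groups had already consented to a randomized trial. Families who declined are not mentioned.

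**The case against.** Several points can fairly be made for the plan.

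- *The target and the period are stated.* A pilot with 8 families would visibly miss its own aim, and the analysis section promises a summary of screening and recruitment. That is true, but neither the aim nor the summary carries a threshold, and the decision to proceed is tied to the criteria.
- *Agreement is not given before all screening.* A case-note screen precedes the invitation, so some ineligible children are removed early. This stands. The gap concerns the vocabulary, speech and PTC checks, which follow consent, and the 20 to 50% range has no support in the article.
- *The criteria come from a similar pilot, and the planned trial is multi-center.* A single-center count would inform that trial only indirectly. This limits how much an accrual criterion can tell the sponsor. It does not rescue a rule that passes with 6 children.
- *Refusals are counted.* A reader might infer that the criteria cannot detect refusal over randomization. The documents do not support that: a family that refuses for this reason has not agreed, and so lowers the recruitment rate. With 53 families, 40 agreeing is 75.5% and passes; 39 is 73.6% and fails. Only refusal by up to a quarter of families, for whatever reason, is compatible with a pass.
- *The questionnaire text is about the interventions.* A reader might also infer that families who refuse are never asked about randomization. The article does not say when or to whom that question is put, and the full protocol or the data collection forms may say more. The secondary point therefore rests on an inference; the main point does not.

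**Conclusion.** The recruitment criterion is a faulty decision rule as worded, and should be changed. That conclusion needs no assumption: followed exactly, 6 of 8 families agreeing is a pass with at most 6 of 40 randomized, and no other criterion would stop it on numbers or time. How far agreement overstates recruitment depends on the post-consent ineligibility rate, which the article does not give. At an assumed 20 to 50%, the identified families needed rise from 54 to between 67 and 107.

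The acceptability point is weaker. On what the article describes, the rating comes from families already willing to be randomized, so it cannot by itself settle the question that the Discussion leaves open. It does not follow that the 75% rating should be recalculated with decliners added: their reasons are unknown, and adding only those who objected to randomization would bias the rate downward.

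**What to change.** 1. Add a go/no-go criterion on the number of children randomized within the two-year window, relative to the target of 40. As an illustration, 30 of 40 would be 75%. The sponsor must choose the threshold, because the plan does not apply its 75% to accrual.
2. Define *identified* as families invited after the case-note screen. This denominator can be counted. A denominator of eligible families cannot, since full eligibility is unknown for those who decline.
3. Report both agreed/invited and randomized/invited against the criterion, and show post-consent screen failures separately.
4. Interpret the randomization-acceptability rating beside the refusal rate and any optional reasons given for declining. Report those separately and do not merge them into the 75% denominator.

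Items 1 to 3 need one reworded and one added criterion, and use screening and recruitment data already due to be summarized. An optional reason for declining, if added to the invitation reply, is a tick-box and a minor ethics amendment. The article says that protocol changes go to the registry and the ethics committee, so these would too. The downside is that the stated recruitment rate becomes less favourable.
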